**Methods:**

This 5 year protocol consists of two phases. First, we will finalize development of a robust SBIRT train-the-trainer model, which will include an SBIRT Trainer Manual, Provider Resource Guide, fidelity observational coding system, case vignettes, and a curriculum for ongoing consultation sessions. Materials will be designed to build the capacity of novice trainers to train lay workers to deliver SBIRT with fidelity. Second, we will recruit 24–36 trainers and 900 providers in order to evaluate the effects of the SBIRT train-the-trainer model on trainer- (e.g., fidelity, knowledge), provider- (e.g., SBIRT attitudes, confidence, acceptability), and patient encounter- (e.g., proportion receiving screening, brief intervention, referral to treatment) level variables. Data on patient encounters will be tracked by providers on programmed tablets or scannable paper forms in real-time. Providers will report on SBIRT delivery on an ongoing basis over a 6-months period. Additionally, we will test the hypothesis that trainer-level factors will account for a substantial proportion of variability in provider-level factors which will, in turn, account for a substantial proportion of variability in patient encounter-level outcomes.

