#### Specific aim 3 (Exploratory)

To explore the extent to which the multi-level variables interact. Specifically, we examine the extent to which outcomes measured at the trainer-level predict outcomes measured at the provider-level, and in turn, the degree to which variables measured at the provider-level predict outcomes measured at the patient-encounter level.

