For Aim 3 exploratory analyses, we will test a series of multilevel models in which patient encounters (Level 1) are nested in providers (Level 2) which are nested within trainers (Level 3). Consistent with Raudenbush and Bryk’s multilevel modeling strategy, the proportion of variance to be explained at each level will be examined as an initial step [63]. Next, following a decomposed-first strategy that advocates for starting with moderation-focused hypotheses to avoid biases associated with conflated effects, we will conduct multilevel regressions testing the extent to which any putative covariates significantly moderate the hypothesized relationship among the variables [64]. We will test putative covariates (e.g., years of experience, biological sex, population group) at two levels: trainer and provider. All tests of moderation will adjust for the multi-level nature of the nested variables. If moderation is not found (e.g., if biological sex of the trainer does not moderate the effect of fidelity on provider attitudes), covariates will be controlled for as predictors. The goal of these analyses will be to determine the proportion of variance in patient encounter-level outcomes accounted for provider-level outcomes, and the proportion of variance in provider-level outcomes accounted for by trainer-level outcomes, after controlling for putative covariates. These data will help to elucidate mechanisms of action underlying the train-the-trainer cascading model.

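### Aim 3 plans two adjacent links but no estimate of whether trainer fidelity or knowledge relates to patient encounters, so the links alone cannot support a statement about the cascade's mechanism

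*Protocol article*

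**What the plan says.** Three places in the protocol article describe the same two steps.

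- **Abstract, Methods.** The hypothesis is that "trainer-level factors will account for a substantial proportion of variability in provider-level factors which will, in turn" explain patient encounter-level outcomes.
- **Specific aim 3 (Exploratory).** First, "we examine the extent to which outcomes measured at the trainer-level predict outcomes measured at the provider-level"; then, "the degree to which variables measured at the provider-level predict outcomes measured at the patient-encounter level".
- **Analysis plan, Aim 3 paragraph.** The goal has two parts. For encounters, the quantity sought is "the proportion of variance in patient encounter-level outcomes accounted for provider-level outcomes". For providers, it is "the proportion of variance in provider-level outcomes accounted for by trainer-level outcomes". Both are adjusted for covariates.

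The models have three levels, with encounters within providers within trainers. Before any predictors enter, "the proportion of variance to be explained at each level will be examined as an initial step". The one worked example of moderation, fidelity acting on provider attitudes, is again an adjacent link. The paragraph closes: "These data will help to elucidate mechanisms of action underlying the train-the-trainer cascading model".

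The Provider-level measures section lists attitudes, confidence, acceptability, appropriateness and feasibility, all self-rated. Provider skill and provider knowledge are not listed there as outcomes.

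**The concern.** The closing sentence is about the whole cascade, from trainer to provider to patient encounter. The two planned quantities each cover one step. A trainer effect that reaches patients through providers is a product of two slopes, and the second must hold between trainers: providers of better trainers must, because of the trainer, deliver more SBIRT. The provider-to-encounter association as described does not isolate that part. It can arise almost entirely because some providers of a given trainer are keener than others, which says nothing about the trainer.

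The second gap runs the other way. The curriculum gives much of its time to the AUDIT risk algorithm and to SBIRT role play, so a good trainer may plausibly change practice through skill. Such an effect need not pass through the provider perception scales, and the plan would then not attribute it to fidelity or knowledge.

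At stake is the interpretation of an exploratory aim. The protocol presents its trainer fidelity measure as an innovation, and the plan does not ask whether that measure relates to what happens in patient encounters.

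**Working it through.** **Plan's own figure.** None is given for Aim 3. The only sample-size basis is 488 for the Aim 2 change in referral (10% to 15%, correlation 0.3). The usual formula for correlated proportions gives 482, so that figure is reproduced closely, but it does not bear on this point.

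**Inputs from the protocol.** There are 24–36 trainers and 900 providers (Participants), so 900/36 = 25 to 900/24 = 37.5 providers per trainer. All effect sizes below are assumptions. Outcomes were simulated as continuous at provider level.

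**Step 1: what a pooled slope measures.** Let ICC be the trainer share of variance in a provider scale. The pooled provider-to-encounter slope is then

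b(pooled) = (1 − ICC) × b(within) + ICC × b(between).

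With ICC = 5–10%, the within-trainer slope has weight 0.90–0.95. A trainer random intercept shifts the weight further that way. If b(between) = 0, the pooled slope is still 90–95% of b(within). The effect carried from trainer to encounter through the scale is a × b(between) = 0, where a is the trainer-to-provider slope.

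**Step 2: simulation, 30 trainers × 30 providers, 3,000 trials per scenario.**

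| Scenario | Planned links | Fidelity to encounter, tested directly |
|---|---|---|
| (a) Fidelity drives half of the between-trainer attitude variance; only within-trainer attitude differences drive reach (r = 0.3) | both significant: 96.9% (ICC 10%), 90.7% (ICC 5%) | 4.7% |
| (b) Fidelity drives 60% of the between-trainer reach variance (ICC 5%) by an unmeasured route | first link significant: 4.4% | 95.9% |

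**Step 3: second simulation, other effect sizes, 24 × 37, 30 × 30 and 36 × 25, 1,500 runs each.** The assumed effects were a = 0.4, b(within) = 0.4 and a direct effect of 0.3. Residual trainer SD was 0.15 for both the scale and the outcome, and the provider-level SD was 1.

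- **A, no trainer effect on encounters.** Scale variance is 0.4² + 0.15² + 1 = 1.1825. Outcome variance is 0.4² + 0.15² + 1 = 1.1825. Expected R² is 0.16/1.1825 = 0.135 for link 1 and 0.16/1.1825² = 0.114 for link 2 (simulated: about 0.13 and 0.12). Both links were significant in 100% of runs, and the direct test in 7–8%.
- **B, effect outside the scales.** Expected direct R² is 0.09/(0.09 + 0.0225 + 1) = 0.081. The links were significant in 6–8% and about 5% of runs, and the direct test in 100%.
- **C, genuine full chain (b(between) = 0.4).** Both links were significant in 100% of runs, and the direct test in 85–92%.

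On the two links alone, A and C look the same, and B looks like nothing.

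**Step 4: what the variance partition adds.** An F test for trainer variance in reach flagged scenario (b) in 96–97% of trials. It stayed at about 4–5% in scenario (a) if reach has no other trainer source of variance. With another trainer source present (Step 3), trainer means still varied by 4.4–5.6% of total variance in A against 6.6–7.9% in C, so the contrast is weaker.

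**Step 5: precision of a direct trainer-to-encounter estimate.** By Fisher's z, power = Φ(atanh(r) × √(k − 3) − 1.96), with k trainers.

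| k | power at r = 0.3 | power at r = 0.5 | r for 80% power |
|---|---|---|---|
| 24 | 29% | 71% | 0.55 |
| 30 | 36% | 81% | 0.49 |
| 36 | 43% | 88% | 0.45 |

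**The case against.** The analysis matches the aim as written: two questions are asked and two are analysed. The aim is exploratory, the closing sentence says only that the data will help, and a condensed article may leave the exact predictor set to a fuller document. That settles how much weight the point deserves. It does not remove it, because the article states both the goal of the analysis and the inference to be drawn, and the second goes further than the first.

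The variance partition is a real safeguard and deserves credit. In scenario (b) it signals a trainer contribution about as often as the direct test does. What it cannot do is say whether that contribution belongs to fidelity, to knowledge or to something else about the trainer.

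The plan also adopts a strategy meant to avoid conflated effects. That might lead to a within- and between-trainer split of provider scores, which would weaken scenario (a). As described, though, the strategy introduces moderation tests of covariates, and no such split is written.

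The scenarios are deliberately extreme: a between-trainer slope of exactly zero, or no passage through the scales at all. They show what is possible, not what is likely. Certification on a benchmark role play may also narrow the range of fidelity and make any direct estimate less precise.

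A reader might infer that Aim 3 could declare a working cascade where trainers have no effect, or reject a real one. The documents do not support that. There is no rule that declares or rejects a cascade. If trainers had no effect on providers either, the first link would be null. A missed route would often show in the partition.

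**Conclusion.** The point holds in limited form. The two planned associations do not establish that trainer fidelity or knowledge reaches patient encounters, and an effect outside the measured provider perceptions would not be attributed to either. Under the assumed effects, both links are significant in 91–100% of simulated trials with no trainer effect on encounters. An effect by an unmeasured route leaves the first link at 4–8%. These figures rest on chosen effect sizes, continuous outcomes and pooled provider slopes. The planned partition lessens the problem without closing it. The consequence is a possible overstatement in an exploratory aim. No primary analysis is affected, and the change is a cheap improvement.

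**What to change.** In the Aim 3 paragraph of the Analysis plan, enter trainer fidelity (as a graded score) and knowledge as Level 3 predictors of each encounter outcome in the three-level model already planned. Fit it first without the provider scales, then with them, each split into trainer mean and within-trainer deviation. Report the total association and its change between the two fits, with confidence intervals, as exploratory estimates.

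Do not make the interpretation depend on significance: at a trainer-level r of 0.3, power is only 29–43%, so a significance gate could dismiss a real cascade. Word the conclusion as two separate associations unless these estimates support a path from trainer to encounter.

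The cost is one extra set of predictors and no new data. The drawback is wide intervals with 24–36 trainers, which should be stated with the result.

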### Power analysis and sample size

We used data from our preliminary pilot work to formulate a realistic range of necessary assumptions for sample size and power considerations for primary outcomes (Table 3). Using our most conservative assumptions that rates of referral to treatment will only increase by 5% (at the lower end of rates reported in our preliminary study) and that the repeated measure correlation is only 0.3, we would need a complete sample of 488 to have sufficient power achieve power of 0.80 with a two-tailed alpha of 0.05. We expect an attrition rate of 20% over time (our prior studies in South Africa have attained retention rates of 85–100%): if we were to conservatively assume an attrition rate twice as high as expected (40%), we would need a sample of 683 to have adequate power. The proposed sample size of 900 is therefore extremely well powered to detect change in rates of screening, brief intervention, and referral to treatment over the course of the study. We propose 900 because it will increase our power to detect significant moderators: power will vary based upon the specific hypothesis and will be calculated using PowerUp! Software [65], but should be adequate to detect moderator effects at the provider- and provider encounter-level data. In addition, our proposed sample is reflective of the South Africa International TTC’s intention to roll out SBIRT nationally and train large cadres of health professionals and lay workers.

**Table 3 Tab3:** Power analysis and sample size (power = .80, alpha = .05)

	Repeated measure correlation	Pre-training rate	Post-training rate	△	Sample Size	
Screening	0.3	25%	40%	15%	107	
		25%	50%	25%	41	
		25%	60%	35%	22	
	0.5	25%	40%	15%	77	
		25%	50%	25%	30	
		25%	60%	35%	16	
Brief Intervention	0.3	20%	40%	20%	58	
		20%	50%	30%	28	
		20%	60%	40%	16	
	0.5	20%	40%	20%	43	
		20%	50%	30%	21	
		20%	60%	40%	13	
Referral to Treatment	0.3	10%	15%	5%	488	
		10%	20%	10%	142	
		10%	25%	15%	71	
	0.5	10%	15%	5%	353	
		10%	20%	10%	104	
		10%	25%	15%	53	

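### The attrition-adjusted sample size of 683 is wrong: keeping 488 completers at 40% attrition takes 814 providers, and 683 would give about 73% power, not 80%

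*Protocol article*

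**What the plan says.** The statement is in the protocol article, section *Power analysis and sample size*, and its accompanying Table 3.

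- The driving scenario is the most demanding row of Table 3: referral to treatment rising from 10% to 15%, where "the repeated measure correlation is only 0.3".
- For that row the text says "we would need a complete sample of 488 to have sufficient power achieve power of 0.80 with a two-tailed alpha of 0.05".
- On losses it says "We expect an attrition rate of 20% over time", and notes that the team's earlier South African studies retained 85–100%.
- It then doubles the expected loss as a stress case: if attrition were "twice as high as expected (40%), we would need a sample of 683 to have adequate power".
- From this it concludes that the planned 900 has very ample power for change in screening, brief intervention and referral, and that the surplus also helps with tests of moderators.

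**The concern.** The 488 is described as a complete sample, so the adjusted figure should be the number to enrol so that 488 remain after the stated loss. A 40% loss from 683 does not leave 488. The printed number is close to what results from adding 40% to 488, a common slip in attrition adjustment.

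Two things depend on it. First, 683 is the only attrition-adjusted requirement that the article prints, so it is the figure a reader would use to judge whether a shortfall in rollout is tolerable. Second, the article's conclusion about 900 is drawn directly from the comparison with 683. If the requirement is higher, the reserve is smaller than claimed.

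**Working it through.** **Inputs, all from the power section and Table 3:** pre-training rate p₁ = 0.10, post-training rate p₂ = 0.15, repeated-measure correlation r = 0.3, two-sided alpha 0.05, power 0.80, complete sample 488, expected attrition 20%, stress-case attrition 40%, stated adjusted sample 683, planned sample 900.

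**Step 1. Does 488 reproduce?** The article names no formula, so three standard ones for paired proportions were tried. The variance of the paired difference is

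V = p₁(1−p₁) + p₂(1−p₂) − 2r√[p₁(1−p₁)p₂(1−p₂)] = 0.0900 + 0.1275 − 0.6 × 0.1071 = 0.1532.

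| Formula | Required n |
|---|---|
| Wald paired difference: (1.960 + 0.842)² × V / 0.05² | 481.1, so 482 |
| McNemar type: [1.960√(V + 0.05²) + 0.842√V]² / 0.05² | 486.5, so 487 |
| Logit scale, as in a GEE model | 489.7, so 490 |

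All three lie within 3% of 488. The base figure is sound, and it reproduces with no term for clustering of providers within trainers.

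**Step 2. Does 683 reproduce?** With attrition d, the number to enrol N must satisfy N(1 − d) ≥ 488.

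- At d = 0.40: N = 488/0.60 = 813.3, so **814**.
- At d = 0.20: N = 488/0.80 = **610**.
- The printed figure: 488 × (1 + 0.40) = 683.2, which rounds to **683**.

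The match with 488 × 1.40 identifies the source of the error. The shortfall is 814 − 683 = 131 providers.

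**Step 3. What would 683 deliver?** 683 × 0.60 = 409.8, about 410 completers, which is 488 − 410 = 78 too few. Scaling from the article's own 488, power is Φ(√(n/488) × 2.802 − 1.960). For n = 410 this is Φ(0.608) = 0.728. The three formulas of Step 1 give 0.727 to 0.734. The largest attrition at which 683 still leaves 488 completers is 1 − 488/683 = 28.5%.

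**Step 4. What does the planned 900 deliver?**

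| Attrition | Completers from 900 | Power, referral 10% to 15% | Required enrolment | Margin of 900 |
|---|---|---|---|---|
| 20% (expected) | 720 | about 0.93 | 610 | 290 |
| 40% (stress case) | 540 | about 0.84 | 814 | 86 (11%) |

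Measured against the printed 683, the margin would be 217 (32%). The 900 keeps 488 completers up to attrition of 1 − 488/900 = 45.8%.

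**The case against.** The strongest reply is that nothing in the design rests on 683. The *Participants* section sets at least 300 providers for each of three organizations, and the *Analysis plan* gives 900 as a minimum. The 683 appears once, in a deliberately pessimistic scenario, and no text allows recruitment to stop there. At the expected 20% attrition 610 providers suffice, so 683 would be enough. This stands: it limits the practical harm, and the scenario of recruitment ending near 683 is hypothetical.

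It can also be said that the claim of very ample power is fair for two of the three outcomes. Table 3 needs at most 107 completers for screening and 58 for brief intervention, against 540 remaining even at 40% attrition. This also stands, on the table's inputs. The overstatement concerns the smallest referral effect combined with doubled attrition, so the correction should be worded by outcome.

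A third point is that the *Analysis plan* includes all trained providers, imputes missing data and uses longitudinal models, so a complete-case power of 0.73 is not exactly the power of the planned analysis. That is true of the 0.73, but it does not rescue 683. The power section makes no use of imputation, asks explicitly for complete cases, and prints a figure that follows only from the wrong operation.

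**Conclusion.** The concern holds. At 40% attrition the requirement is 814, not 683. With 683 enrolled, power for referral rising from 10% to 15% would be about 0.73 instead of 0.80.

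The planned 900 remains sufficient on the article's own inputs, with about 0.84 power at 40% attrition and about 0.93 at 20%. The error is therefore a false stated requirement and an overstated reserve, not an underpowered design.

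The 814 rests only on the article's 488 and 40%. The power values are this review's own. They further assume a complete-case comparison of two time points, with the rates and correlation in Table 3 and no allowance for clustering. The *Analysis plan* describes providers as nested within trainers, but Table 3 lists no intraclass correlation. In the stress case, the 11% margin is thus the only visible reserve for anything that calculation leaves out.

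**What to change.** In *Power analysis and sample size*:

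1. Replace 683 with 814, and show the formula: 488/(1 − 0.40).
2. Add the figure for the expected 20% attrition: 488/(1 − 0.20) = 610.
3. Replace the general claim about 900 with the margin by outcome. For example: *With 900 providers enrolled, 720 would remain at 20% attrition and 540 at 40%. For an increase in referral from 10% to 15% with correlation 0.3, this gives power of about 0.93 and 0.84 under the assumptions used for Table 3. The screening and brief intervention scenarios in Table 3 need at most 107 and 58 completers.*

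Before the power values are printed, they should be confirmed with the method that produced Table 3. The cost is one corrected number and two or three sentences. Enrolment, design and analysis do not change.

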## Analysis plan

Aim 1 (creation of a Trainer Manual) will not require formal data analysis. For Aim 2, all SBIRT trainers (n = 24–36) and all providers who receive SBIRT training (minimum n = 900) will be included in the statistical analyses [57, 58]. Prior to the main analyses, we will run descriptive statistics on the outcomes collected as part of Aim 2 to examine distributional properties, identify outliers, and transform variables as needed. Missing data will be imputed following recommendations of the National Research Council [59]. We will test the appropriateness of assumptions underlying the use of multiple imputation using sensitivity analyses [60].

For Aim 2 evaluation of trainer outcomes, the proportion of training sessions that met the fidelity benchmark will be examined as an outcome of interest, with the goal that at least 80% will meet the target. In addition, we will examine pre-training to post-training change in trainer SBIRT knowledge and proportion of trainers who attained the 70% knowledge benchmark immediately at the culmination of training.

For Aim 2 evaluation of provider- and patient encounter-level variables, change in each outcome will be examined over three distinct time intervals: 3-months pre-training to training (i.e., baseline reports of the past 90 days); training to 3-months post-training; and 3- to 6-months post-training. We will use longitudinal models to examine whether the provider- and patient encounter-level implementation outcomes significantly change across 3 assessments. Repeated measures and nested structures (due to providers being nested within trainers) will be accounted for by adding appropriate random effect terms. The longitudinal models will be estimated using generalized estimation equations which lead to robust standard error and statistical inferences [61]. Using the models, we will examine the outcomes of each post-training visit and compare them with the pre-training outcome. An omnibus test also will be conducted to compare all post-training visit outcomes with the pre-training outcomes. In addition to reporting statistical significance, we will report the effect size using Cohen’s d [62].

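### Table 3's power is computed for independent providers with one yes/no response before and after training, not for providers nested in 24–36 trainers whose outcome is a proportion of encounters

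*Protocol article*

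**What the plan says.** The section on power analysis and sample size takes as its most conservative case a rise in referral from 10% to 15% and assumes that "the repeated measure correlation is only 0.3". It states that "we would need a complete sample of 488" for "power of 0.80 with a two-tailed alpha of 0.05". It then notes "We expect an attrition rate of 20% over time", doubles that to 40% as a cautious case, arrives at 683, and concludes: "The proposed sample size of 900 is therefore extremely well powered to detect change in rates" of screening, brief intervention and referral to treatment.

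The inputs shown are pre- and post-training rates, a repeated-measure correlation of 0.3 or 0.5, alpha and power. No intraclass correlation, number of trainers, cluster size or number of encounters per provider enters the calculation. PowerUp! is named only for later moderator power.

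Elsewhere the article describes a different structure:
- Participants: 900 providers are trained by 24–36 trainers in three organizations.
- Analysis plan, Aim 2: "Repeated measures and nested structures (due to providers being nested within trainers) will be accounted for".
- Patient encounter-level measures: reach is the proportion of a provider's encounters in which the service was delivered, not a single response.

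**The concern.** The power statement should describe the analysis that will be run. If trainers differ in how much their providers change, providers under one trainer are not independent, and 900 providers carry less information than Table 3 assumes. Trainers deliver the intervention, so differences between them can act on the change itself.

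The exposure is greatest for referral, which the claim names explicitly and whose 5-point row is the one carried forward to 488 and 683. A small referral effect is also realistic: the pilot section reports a move from 15% to 18%. If the claim stands as written, a non-significant referral result could be read as good evidence of no change, on the strength of a calculation that does not match the design.

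**Working it through.** **Inputs from the article.** Two-sided alpha 0.05; power 0.80; referral 10% to 15%; correlation r = 0.3; 900 providers; 24–36 trainers; attrition 20% or 40%. Completers: 900 × 0.8 = 720 and 900 × 0.6 = 540.

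**Assumed, because the article gives no value.** Trainer ICC of the pre-post change (0 to 0.10), encounters per provider, and within-provider correlation.

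**1. Reproducing Table 3.** Take s = √(p(1−p)) rounded to two decimals, the variance of the change as s1² + s2² − 2·r·s1·s2, and a paired t-test with N − 1 degrees of freedom. For 10% to 15%, r = 0.3: s1 = 0.30, s2 = 0.36, variance = 0.0900 + 0.1296 − 2(0.3)(0.30)(0.36) = 0.1548, giving N = 488. The same recipe returns the printed N in all 18 rows. This leaves no room for a clustering term, and each provider counts as a single yes/no response at each time.

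**2. Adding the trainer level, keeping Table 3's variance.** Design effect = 1 + (m − 1) × ICC, where m is completers per trainer; effective N = completers / design effect; power from the noncentral t with trainers − 1 degrees of freedom.

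Example: 720 completers, 24 trainers, ICC 0.05. m = 30, design effect = 1 + 29 × 0.05 = 2.45, effective N = 720 / 2.45 = 294, power 0.55. With 36 trainers: m = 20, design effect 1.95, effective N = 369, power 0.66.

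Power for referral 10% to 15%, r = 0.3 (24 to 36 trainers):

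| ICC of change | 720 completers | 540 completers |
|---|---|---|
| 0 | 0.90–0.91 | 0.81–0.82 |
| 0.01 | 0.82–0.86 | 0.73–0.77 |
| 0.02 | 0.74–0.81 | 0.66–0.72 |
| 0.05 | 0.55–0.66 | 0.50–0.60 |
| 0.10 | 0.38–0.50 | 0.36–0.46 |

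**3. Break-even ICC.** Effective N equals 488 when ICC = (completers/488 − 1)/(m − 1).
- 20% attrition: (720/488 − 1)/29 = 0.016 with 24 trainers; 0.4754/19 = 0.025 with 36.
- 40% attrition: (540/488 − 1)/21.5 = 0.005; 0.1066/14 = 0.008.

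Trainer-based degrees of freedom lower these thresholds somewhat further.

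**4. The other rows, same method, at the harshest setting (540 completers, 24 trainers, ICC 0.10).** Screening 25% to 40%, r = 0.3: 0.93. Brief intervention 20% to 40%, r = 0.3: above 0.99. Referral 10% to 20%, r = 0.3: 0.84. The 5-point referral row with r = 0.5 is intermediate: 0.86–0.91 at ICC 0.02 and 0.69–0.80 at ICC 0.05, with 720 completers.

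**5. The opposite correction: averaging over encounters.** With k encounters per provider and within-provider correlation ρ, the single-response variance is multiplied by ρ + (1 − ρ)/k. For assumed k = 30:
- ρ = 0.3: factor 0.3 + 0.7/30 = 0.32. Power in the 5-point row is 0.93–0.99 at ICC 0.05 and 0.80–0.93 at ICC 0.10, across both attrition rates.
- ρ = 0.5: factor 0.52. Power is 0.78–0.91 at ICC 0.05 and 0.60–0.77 at ICC 0.10.

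These figures take the ICC relative to the reduced variance. Averaging does not shrink the trainer component itself. If instead an ICC of 0.05 refers to the single-response variance, then with factor 0.323 and 720 completers the effective N is 1/(0.273/720 + 0.05/24) = 406 with 24 trainers and 1/(0.273/720 + 0.05/36) = 565 with 36. That straddles 488, so the answer turns on quantities the article does not give.

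**The case against.** The strongest reply is that the damage is confined to one effect size and may be cancelled. Step 4 shows that the claim survives for two of the three outcomes and for referral changes of 10 points or more. Step 5 shows that the variance behind the low figures is probably too large for a proportion taken over six months of encounters. The planned analysis already allows for nesting, so the inference is not at risk, and 900 is also justified by moderator power and the national rollout. All of this stands. It limits the point to the power statement and to small referral changes.

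A reader might go further and infer that the study has only about even odds of detecting the 5-point referral change. The documents do not support that: the figure needs an assumed ICC of about 0.05 or more together with Table 3's single-response variance, and the article gives neither an ICC nor encounter counts.

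A reader might also say that the calculation contradicts the article's hypothesis that "trainer-level factors will account for a substantial proportion of variability in provider-level factors". That is too strong as well. The abstract's examples of provider-level factors are attitudes, confidence and acceptability; reach is an encounter-level outcome, linked to trainers only through providers. Stable differences between trainers or sites largely cancel in a pre-post contrast. The hypothesis makes an ICC of exactly zero hard to defend, but it fixes no value for the change in referral.

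What the reply does not remove is the mismatch. Table 3 differs from the planned analysis in both clustering and outcome, and nothing in the article shows that the two departures balance.

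**Conclusion.** The point holds in a limited form. It is certain that Table 3 omits clustering by trainer and uses a single-response variance, since every row reproduces exactly on that basis. The stated 0.80 power at 488, and the reserve claimed at 900, are therefore not computed for the planned design.

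The size of the consequence is conditional. On Table 3's variance, the 5-point referral case loses its margin at a small trainer ICC of change: about 0.02 at the expected attrition and below 0.01 at the article's own cautious attrition. Screening, brief intervention and larger referral changes are not threatened over the range tried. Once encounters are averaged, the 5-point case could end above or below 0.80. The unqualified claim for referral is thus unsupported, but it is not shown to be false.

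**What to change.** Recompute Table 3 for the analysis that is planned:
- Use the provider-level proportion as the outcome, with a stated range for encounters per provider and within-provider correlation.
- Apply 1 + (m − 1) × ICC for a range of ICC of change, for example 0.01–0.10, with 24–36 trainers and trainer-based degrees of freedom. State which variance the ICC refers to.
- Report power or the minimum detectable change at 900 enrolled, at 20% and 40% attrition.
- Limit the strong power claim to the outcomes and effect sizes for which it holds, and give the 5-point referral case its own figure.

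The cost is one recalculation and a rewritten paragraph, with a possibly less favourable figure for small referral changes. Enrolment, procedures and the planned analysis stay as they are.
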